#### Secondary study parameters

All secondary study parameters will be compared using the appropriate tests, which are subsequently adjusted for age, sex and amputation level. Categorical variables will be analysed using the χ^2^ test or Fisher’s exact test and adjusted with a logistic regression model. Continuous variables will be assessed using the Student’s t-test or Mann-Whitney U test and adjusted using a linear regression model.

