### Outcomes

Longitudinal studies show no further improvement of PAP after TMR in amputees after 12 months postoperatively.^15 23 26 27^ Therefore, our follow-up time will be 12 months. Outcomes will be assessed at 2 weeks and at 3, 6, 9 and 12 months via questionnaires (table 1). These will be completed digitally via email, using a pseudo-anonymised data management platform. Patients allocated to the control group who experience significant pain at the end of the study will be offered additional TMR, regardless of amputation level.

**Table 1 T1:** Schedule of enrolment PreventPAP trial

Study period	Enrolment	Allocation	Postallocation						Close-out
Timepoint in Months	0	0	0.5	3	6	9	11	12	12
Enrolment:									
Screening/eligibility criteria	X								
Informed consent	X								
Allocation		X							
Assessment:									
Baseline characteristics	X	X							
Preoperative/intraoperative/postoperative variables	X	X							
Questionnaires:									
NRS RLP and PLP*				X	X	X		X†	
PROMIS Pain Behaviour 7a Short Form^29^				X	X	X		X†	
PROMIS Pain Interference 8a Short Form^29^				X	X	X		X†	
EQ-5D-5L^32^			X	X	X	X		X	
ICAN Pain Sketches^30^				X	X	X		X	
iMCQ and iPCQ^36 37^				X	X	X		X	
PainDetect^31^								X	
HADS^33^								X	
GPE-DV^34^								X	
PLUS-M^35^								X	
Close-out:									
Outcome									X
Medication‡									

* NRS for RLP and PLP will be measured every day for 30 consecutive days at 11 months postamputation.

† Primary endpoint.

‡ Medication will be recorded at the end of the study for the whole study period.

EQ-5D-5L, European Quality of Life - 5 Dimensions - 5 Levels; GPE-DV, Global Perceived Effect - Dutch Version; HADS, Hospital Anxiety and Depression Scale; ICAN, Interdisciplinary Care for Amputee Network; iMCQ, Medical Consumption Questionnaire; iPCQ, Productivity Cost Questionnaire; NRS, Numeric Rating Scale; PLP, phantom limb pain; PLUS-M, Prosthetic Limb Users Survey of Mobility; PROMIS, Patient-Reported Outcomes Measurement Information System; RLP, residual limb pain.

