#### Secondary study parameters/endpoints

Secondary endpoints include the use of analgesics or pain interventions, surgical time, length of hospital stay and adverse events or complications, including survival. In addition, multiple questionnaires will be sent to the participants regarding RLP and PLP during the study (measured by the NRS); pain behaviour and pain interference during the study (measured by the PROMIS Pain Behaviour and Pain Interference Short Forms)^29^; local, diffuse or radiating pain (measured by the Interdisciplinary Care for Amputee Network pain sketches)^30^; neuropathic pain (measured by the PainDetect)^31^; quality of life (measured by the European Quality of Life - 5 Dimensions - 5 Levels (EQ-5D-5L))^32^; anxiety and depression symptoms (measured by the Hospital Anxiety and Depression Scale)^33^; perceived treatment effect (measured by the Global Perceived Effect - Dutch Version)^34^ and mobility 1 year after surgery (measured by the Prosthetic Limb Users Survey of Mobility).^35^ A cost-effectiveness analysis (CEA; measured by the Medical Consumption Questionnaire (iMCQ))^36^ and the Productivity Cost Questionnaire (iPCQ)^37^ and a budget impact analysis (BIA) (measured by the ZonMw BIA tool) will also be performed at the end of the study. All data will be collected using validated questionnaires at different time points (table 1).

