### Sample size calculation

In studies of both chronic and acute pain, a change of two points on the NRS has been shown to be clinically relevant and correlated to a patient’s need to take additional pain medication.^38^ To detect a minimal clinically important difference of two points on the NRS, considering an SD of 3.5 from similar studies that measured pain at one time point after 12 months^15 23 26 27^ in a clinically heterogeneous group, with a significance level of 0.025, we need to analyse 2×76=152 patients to achieve 90% power. With an estimated loss to follow-up of 6%, we need to include 162 patients. Moreover, based on the study by Cascini *et al*^25^ and our clinical experience, we expect a 1-year mortality rate of 20% in our patient population aged 75 years or younger. With an estimated 1-year survival of this patient group of 80%, we need to include 203 patients in total. Due to the semiacute setting of most amputations, organising the availability of both extra operating time and a trained nerve surgeon might be a challenge. Therefore, we estimate including 40% of all major lower extremity amputations. To be able to randomise 203 subjects, we estimate the need to screen 508 patients (figure 2).

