### Statistical analysis

Continuous variables will be summarised by treatment group using the number of non-missing data points, mean, SD, median and IQR. Categorical and ordinal variables will be summarised by treatment group based on observed frequencies and percentages relative to the total number of non-missing items. To account for the correlation between measurements within the same patient, a repeated measures analysis will be conducted. This will allow us to include all participants with at least a single follow-up measurement. Where appropriate, we will include age, sex and amputation level in our analyses.

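### Length of hospital stay is left to a t-test or Mann-Whitney test with no handling of death before discharge, so unequal in-hospital mortality would favour the arm with more deaths

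*Protocol article*

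**What the plan says.** The section on secondary study parameters/endpoints of the protocol article lists "surgical time, length of hospital stay and adverse events or complications, including survival".

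Under Statistical analysis, the subsection on secondary study parameters opens with a general rule: "All secondary study parameters will be compared using the appropriate tests, which are subsequently adjusted for age, sex and amputation level". It then names two routes. Categorical variables go to a χ² test or Fisher's "exact test and adjusted with a logistic regression model". Continuous variables go to Student's "t-test or Mann-Whitney U test and adjusted using a linear regression model".

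The article names no time-to-event or competing-event method and gives no rule for a patient who dies before discharge. On mortality, the sample size section says only "we expect a 1-year mortality rate of 20% in our patient population aged 75 years or younger". The Outcomes section fixes the same observation period for everyone: "Therefore, our follow-up time will be 12 months". Categorical summaries use "observed frequencies and percentages relative to the total number of non-missing items".

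**The concern.** A hospital stay ends in one of two ways, discharge alive or death. A rule for continuous variables sees only the number of days. A patient who dies on day 3 then contributes 3 days, the same as a patient who goes home well on day 3, and both pull the arm towards a shorter stay. The linear regression adjusted for age, sex and amputation level has the same defect.

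This matters in this trial because the population has substantial mortality and the TMR procedure adds 30–90 min of surgery. The article itself links an increase of that length to a slightly higher infection risk, and no data safety board is assigned. Length of stay is one of the few resource and recovery outcomes reported by arm. A measure that improves as deaths rise is a poor choice there, and a suitable alternative costs little.

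**Working it through.** **1. What the 20% covers.** The plan's own figures reproduce: 152/0.94 = 161.7, rounded to 162, and 162/0.80 = 202.5, rounded to 203. The 20% is therefore a 1-year rate, giving 0.20 × 203 = 40.6 expected deaths. Only deaths before discharge affect length of stay, and the article does not give that share. All in-hospital rates below are assumptions.

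**2. Mean shift from deaths alone.** Both models give the two arms the same underlying time to discharge, so any difference comes from deaths only.

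*Model A:* lognormal time to discharge, median 12 days, log-SD 0.6, with a constant death hazard h per day. The mean observed stay is P(death before discharge)/h.
- Control, h = 0.004: 0.055/0.004 = 13.8 days
- TMR, h = 0.008: 0.106/0.008 = 13.3 days, shift −0.5
- TMR, h = 0.012: 0.153/0.012 = 12.8 days, shift −1.0
- TMR, h = 0.020: 0.237/0.020 = 11.9 days, shift −1.9

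*Model B:* lognormal stay, median 10 days, log-SD 0.7, mean 10 × exp(0.7²/2) = 12.8 days. A proportion q die at a uniformly distributed point of the stay, so the mean observed stay is 12.8 × (1 − q/2).
- 5% against 10%: −12.8 × 0.05/2 = −0.3 day
- 5% against 15%: −12.8 × 0.10/2 = −0.64 day

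**3. How often Mann-Whitney is misled.** Simulation with 4,000 trials per scenario, about 101 per arm, two-sided 0.05. By chance alone, 2.5% of trials should favour a given arm.

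| Model | In-hospital deaths, control vs TMR | Shift in mean stay (days) | Trials declaring a shorter stay in the arm with more deaths |
|---|---|---|---|
| A | equal, 5.5% | 0 | about 2.5% |
| A | 5.5% vs 10.6% | −0.5 | about 6% |
| A | 5.5% vs 15.3% | −1.0 | about 13% |
| A | 5.5% vs 23.7% | −1.9 | about 37% |
| B | equal, 5% | 0 | 2.4% |
| B | 5% vs 10% | −0.3 | 5.3% |
| B | 5% vs 15% | −0.65 | 10.4% |
| B | 10% vs 20% | −0.6 | 8.7% |

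The 23.7% row exceeds the whole expected 1-year mortality and is an extreme, not a planning case. When deaths are ranked worst, the false finding of a shorter stay in the unequal scenarios falls to 1% or less.

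**4. Survival.** If survival is analysed as 12-month status and the 6% lost are dropped, the lost patients number 0.06 × 162.4 = 9.7. The death proportion becomes 40.6/(203 − 9.7) = 21.0% instead of 20.0%. For power, take 101.5 per arm, 20% control mortality and assumed hazard ratios (HR). The log-rank power is Φ(|ln HR| × √(deaths/4) − 1.96).
- HR 0.5: TMR mortality 1 − 0.8^0.5 = 10.6%; 31.0 deaths; log-rank 0.49, χ² 0.46, χ² with 6% dropped 0.44.
- HR 2: TMR mortality 1 − 0.8² = 36%; 56.8 deaths; log-rank 0.74, χ² 0.72, χ² with 6% dropped 0.70.

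The binary analysis therefore costs about 2 to 5 percentage points of power.

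**The case against.** The strongest reply is that the article assigns neither length of stay nor survival to a named test. It promises suitable tests and then gives generic rules, and finer detail may sit in an analysis plan that is not shown. Part of this stands. The article does not say that a death counts as a short stay; that follows only if the continuous rule is applied to observed days. But the general sentence covers every secondary parameter, the sentences after it say which tests are meant, and length of stay fits only the continuous route. The point is thus a stated rule that does not suit a listed endpoint, which goes beyond missing detail.

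Three further objections limit the point.

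- **The 20% is not an in-hospital rate.** A reader might infer that one patient in five would distort length of stay. The article does not support that, and with equal in-hospital mortality there is no average bias at all.
- **Deaths are also compared directly.** A reader might infer that harm would be hidden. Under model A, a χ² test on in-hospital death flags the TMR excess in about 27%, 65% and 97% of trials in the three unequal scenarios. A shorter stay without a mortality signal occurs in only about 4%, 3% and 0.5%, against 2.4% with equal mortality. In the extreme case the harm is almost never concealed.
- **Twelve-month status is a legitimate outcome for survival.** Survival is listed within adverse events or complications, follow-up is a fixed 12 months and expected loss is 6%. The denominator of non-missing items governs descriptive summaries, and patients who stop returning questionnaires need not have unknown vital status.

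**Conclusion.** The point holds for length of stay. As the rules stand, the comparison would tend to favour the arm with more in-hospital deaths whenever those deaths are unequal. With roughly 5% against 10–15% in-hospital deaths, the shift is about 0.3 to 1.0 days, and a misleading Mann-Whitney result arises in about 5–13% of trials instead of 2.5%. These sizes rest on assumed in-hospital rates and assumed lognormal stays, and on observed days being analysed without a rule for deaths. The documents do not show that in-hospital mortality will differ between arms.

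For survival there is only a small loss of information, and the article's approach is usable.

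A reader might also infer that the cost-effectiveness result is compromised. The article does not support this: the economic evaluation compares average costs and QALYs by net benefit and does not rest on the length-of-stay test. Both outcomes lie outside the gatekeeping for the four co-primary endpoints, so the primary conclusion is unaffected.

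**What to change.** In the statistical subsection on secondary study parameters, take length of stay out of the continuous rule and state one of the following, adjusted for age, sex and amputation level:

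- time to discharge alive with in-hospital death as a competing event (cumulative incidence by arm, with a cause-specific or Fine-Gray model);
- days alive and out of hospital over a fixed period, for example 90 days;
- a rank-based comparison with in-hospital deaths placed worst, with an ordinal model for the adjustment.

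Report in-hospital mortality by arm next to the result, whichever is chosen.

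As a minor addition, report survival from randomisation by Kaplan-Meier and a Cox model with the same covariates, censored at the date last known alive, so that patients lost before 12 months still contribute. The expected gain is small.

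The cost is a few sentences and a little programming. The data needed are the dates of randomisation, surgery, discharge, death and last contact, plus readmission dates if days out of hospital is chosen. The downside is a result slightly less simple to read than a mean difference in days.

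### The two-sample-test-plus-regression rule for all secondary outcomes does not fit the repeated-measures plan where a secondary outcome is measured at several visits, and it leaves two results per outcome with no stated priority

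*Protocol article*

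**What the plan says.** Three parts of the protocol article bear on this.

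- **Statistical analysis (opening paragraph).** "To account for the correlation between measurements within the same patient, a repeated measures analysis will be conducted". The stated benefit is inclusive: "This will allow us to include all participants with at least a single follow-up measurement". The paragraph does not name the outcomes it covers.
- **Statistical analysis, Secondary study parameters.** The scope is universal: "All secondary study parameters will be compared using the appropriate tests, which are subsequently adjusted for age, sex and amputation level". For continuous outcomes, a t-test or "Mann-Whitney U test and adjusted using a linear regression model". For categorical outcomes, a chi-square "test or Fisher’s exact test and adjusted with a logistic regression model". Visits, repeated measurements and the ranking of the two results are not mentioned.
- **Outcomes, Secondary study parameters/endpoints, and Table 1.** "Outcomes will be assessed at 2 weeks and at 3, 6, 9 and 12 months via questionnaires". Secondary outcomes include questionnaires "regarding RLP and PLP during the study (measured by the NRS"), and the two PROMIS forms over the same period. Table 1 schedules NRS and PROMIS at 3, 6 and 9 months besides 12, pain sketches at 3, 6, 9 and 12 months, and EQ-5D-5L at 2 weeks and 3, 6, 9 and 12 months. PainDetect, HADS, GPE-DV and PLUS-M appear at 12 months only. Surgical time and length of stay have one value per patient.

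**The concern.** None of the methods named for secondary outcomes handles several values from one patient, and none uses a patient who lacks the value being tested. The opening paragraph gives exactly those two reasons for choosing a repeated-measures analysis. For the longitudinal secondary outcomes, an analyst could follow either text and claim to have followed the protocol.

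A second difficulty affects single-value outcomes too. The rule produces an unadjusted test and then an adjusted regression, without saying which is the inference to report. Where the first step is a Mann-Whitney test, the regression is not an adjusted form of it: one compares ranks, the other means. The two can disagree, and the choice would then be made after seeing both.

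At stake are the clarity and efficiency of the secondary results on pain over time and quality of life, and protection against a post hoc choice between two p-values. The confirmatory tests are not at stake.

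**Working it through.** **1. Which outcomes are affected (Table 1).**

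| Secondary outcome | Visits | Visit-level comparisons |
|---|---|---|
| NRS, RLP and PLP | 3, 6, 9 months (12 is primary) | 2 × 3 = 6 |
| PROMIS, two forms | 3, 6, 9 months (12 is primary) | 2 × 3 = 6 |
| EQ-5D-5L | 0.5, 3, 6, 9, 12 months | 5 |
| Pain sketches | 3, 6, 9, 12 months | 4 |
| Total | | 21 |

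Only 2 of the 21 fall at 12 months (one EQ-5D-5L, one pain sketch). For single-value outcomes a repeated-measures model adds no patients, so there is nothing to reconcile.

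**2. The plan's own sample size and attrition (Sample size calculation).** Inputs: difference 2, SD 3.5, two-sided alpha 0.025, power 90%, loss 6%, mortality 20%.

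- Per arm: n = 2 × 3.5² × (2.241 + 1.282)² / 2² = 76.0, or 77 when rounded up. Power at 76 per arm is 0.8999. The stated 2 × 76 = 152 is reproduced.
- 152 / 0.94 = 161.7, giving 162; 162 / 0.80 = 202.5, giving 203. Both agree with the article.

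**3. Patients with a value at each visit.** At 12 months: 203 × 0.80 × 0.94 = 152.7, about 153. The article gives no timing of deaths and losses. Assuming a constant rate, the number at month m is 203 × (0.80 × 0.94)^(m/12):

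- 3 months: 189
- 6 months: 176
- 9 months: 164
- 12 months: 153

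For an outcome first measured at 3 months, a repeated-measures set is therefore about 189, with 203 as the ceiling if everyone gives at least one value. Against 153 the difference is 189 − 153 = 36 to 203 − 153 = 50 patients. For EQ-5D-5L, first measured at 2 weeks, the same formula gives 203 × 0.752^(0.5/12) = 200.6, inside that range.

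This is a head count, not a gain in precision. The extra patients have earlier values only and inform a 12-month contrast only through their correlation with later values. At 3, 6 and 9 months a separate test would itself use more than 153 patients.

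**4. Two results per outcome.** With each tested at 0.05, the chance under the null that at least one is significant is 1 − P(|Z₁| < 1.96 and |Z₂| < 1.96). It depends on the correlation of the two statistics, which the article cannot give:

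| Assumed correlation | Chance of at least one |
|---|---|
| 0.99 | 0.057 |
| 0.95 | 0.065 |
| 0.90 | 0.070 |
| 0.80 | 0.078 |

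The inflation per outcome is modest. The main problem is that the reported result is undefined.

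**The case against.** The best defence is that the repeated-measures paragraph stands at the head of the statistical section, before the primary and secondary subsections, and is not limited to primary outcomes. The secondary subsection speaks of appropriate tests. Read together, repeated outcomes would get the repeated-measures model and single-value outcomes the two-sample tests and regression. That reading is reasonable, so this is an unclear overlap more than a flat contradiction. It does not remove the point: the secondary subsection claims all secondary parameters and names specific methods, and a specific section would normally govern a general one.

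Several stronger readings are tempting and not supported:

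- A reader might infer that the article prescribes separate complete-case tests at every visit. It mentions neither visits nor complete cases; that is one way of applying the rule, and pooling the visits is another.
- A reader might infer that every secondary outcome loses patients. Single-value outcomes do not.
- A reader might infer that the quality-of-life result in the economic evaluation is weakened. The QALY comparison is by intention to treat with multiple imputation, so only EQ-5D-5L as a clinical outcome is affected.

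It can also be said that the criterion for t-test versus Mann-Whitney and the reporting order are matters for a SAP, that adjusting subsequently hints at the adjusted model as the final step, and that secondary outcomes lie outside the alpha scheme. The first is fair for the test criterion. The other two lower the weight of the point, but a hint is not a rule. Finally, making regression the only inference for everything would go too far: sparse events, skewed data such as length of stay, and survival need other methods. That stands and shapes the fix.

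**Conclusion.** The point holds for the secondary outcomes measured at more than one visit, and in a smaller form for the ranking of unadjusted and adjusted results across secondary outcomes. Taken literally, the secondary rule sets aside either the within-patient correlation or the partly observed patients that the repeated-measures analysis was chosen to handle.

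The size is uncertain. The 12-month figure of about 153 of 203 follows from the plan's own attrition. The 36 to 50 additional patients rest on the constant-rate assumption and the ceiling of 203, and they overstate the information gained at 12 months. The 0.057 to 0.078 range rests on assumed correlations. The co-primary analyses and the sample size do not depend on this rule. It is a correction that should be made, but it does not threaten the confirmatory conclusion.

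**What to change.** Amend the Secondary study parameters subsection of the statistical analysis as follows.

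- **Repeated secondary outcomes.** State that NRS and PROMIS during the study, EQ-5D-5L as a clinical outcome, and pain sketches use the repeated-measures model, with arm, visit, arm-by-visit interaction, age, sex and amputation level, and a logistic version for categorical outcomes.
- **Single-value outcomes.** State that the estimate adjusted for age, sex and amputation level is the reported inferential result, and label the unadjusted tests descriptive.
- **Exceptions.** Keep exact or rank-based methods for sparse or clearly skewed outcomes, by a rule fixed before unblinding. Do not force survival into the linear or logistic rule.

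The cost is wording in the protocol and SAP. No new data, visits or patients are needed, and fewer inferential tests result. The change should be made before unblinding.

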#### Cost-effectiveness analysis (CEA)

The economic evaluation will be a trial-based cost-utility analysis (CUA) from a societal perspective (CUA, ie, costs per quality-adjusted life years (QALYs)). Care with and without TMR will be compared with a 1-year time horizon. Estimated societal costs will include hospital (based on study registrations) and other healthcare and productivity costs, using the iMCQ^36^ and iPCQ^37^ at 3, 6, 9 and 12 months. A cost-price analysis will be performed for the TMR. Other healthcare costs will be valued according to the Dutch reference prices whenever possible, including travel costs without discounting (because of the short time horizon). Productivity losses will be valued using the friction-cost method. QALYs will be calculated using the Dutch tariff for the EQ-5D-5L,^32^ at 2 weeks and at 3, 6, 9 and 12 months. Average costs and QALYs will be compared according to ITT, using net-benefit analysis and multiple imputation to account for missing data. Sensitivity analyses will include the cost perspective (healthcare instead of societal) and the utility measure (European Quality of Life visual analogue scale with power-transformation instead of the EQ-5D-5L). If, contrary to expectations, TMR does not deliver better QALYs at lower costs, mathematical extrapolation will be used to perform a threshold analysis on the time horizon.

